### Randomization

In total, 75 sets of double-blind needles were prepared and placed in separate bags numbered 1-75 (25 sets of 40 penetrating acupuncture needles, 25 sets of 40 skin-touch acupuncture needles, and 25 sets of 40 no-touch acupuncture needles). Seventy-five participants were randomly assigned 1:1:1 to the penetrating needle group, the skin-touch needle group, or the no-touch needle group by an independent investigator using a random numbers table that was generated by the RAND function (Microsoft Office Excel 2007).

### Data Management and Monitoring

The completed paper questionnaires are stored in a locked file cabinet for 10 years. Each participant was anonymized by coding without assigning any personal identification. Data from all outcomes were collected and stored in a database that restricts access by password.

The data manager, who was not directly associated with the study, oversees data monitoring activities throughout the study. Informed consent forms, data entry, completeness, and consistency were checked regularly to ensure data quality and protocol compliance.

### Inclusion Criteria and Exclusion Criteria

#### Inclusion Criteria

A physician from TAU Medical Clinic and a research assistant from TAU Acupuncture Clinic identify eligible participants based on the following criteria: (1) are aged 18-65 years, (2) have a diagnosis of CNSLBP, and (3) have other physical treatments such as physical therapy, massage, or take medications for CNSLBP one week before they are assigned to the treatment group and for the duration of the study.

Concomitant physical therapy, massage, or stable medication use is permitted for ethical and pragmatic reasons, reflecting real-world management of CNSLBP. Participants are instructed not to initiate new treatments during the study period. Randomization is expected to distribute co-interventions evenly across groups, thereby mitigating systematic confounding while preserving external validity.

#### Exclusion Criteria

Participants who have the following are excluded, including infections or tumors of the spine, lumbar herniation, rheumatism, lumbar vertebral compression fracture, scoliosis, osteoporosis, lateral curvature of the spine, central or peripheral neuropathy, sciatica, chronic neuropathic pain, circulatory disturbances of the lower limbs, hemorrhagic disorders, or taking anticoagulant medications, and are pregnant.

### Telephone Screening

The purpose and overview of the study were explained to potential participants over the telephone. They were then screened for eligibility. If participants met the inclusion criteria, they were given an appointment at the TAU Medical Clinic for a physical examination and x-rays to diagnose CNSLBP. Participants were also informed that they can withdraw from the study at any time.

### Baseline Assessment

On the first visit to TAU Acupuncture Clinic, the study’s objectives and methods were explained to participants using a written script. All questions are then answered, and study consents are signed. A physician at TAU Medical Clinic completed a physical examination, and an X-ray of the lumbosacral region of the frontal and sagittal planes was taken to confirm the morphological changes necessary to diagnose CNSLBP. Participants then completed all baseline questionnaires. The intensity of LBP was rated on a 100 mm visual analog scale (VAS) ranging from 0 (no pain) to 100 (most severe pain imaginable). The Roland Morris Disability Questionnaire (RMDQ) assessed physical disability due to LBP and contains 24 statements that described the discomfort that may occur with LBP. Participants were asked to check the responses that best describe their life on that day; the score was based on the total number of statements selected (0-24) [47]. The Japanese version of the RMDQ has been found to be reliable and valid for assessing patients with LBP [48]. The Japanese Orthopedic Association Back Pain Disease Questionnaire (JOABPEQ) assesses physical disability due to LBP and consists of 25 statements in 5 domains (back pain-related disorders, lumbar dysfunction, gait dysfunction, social life disorders, and psychological disorders) for the past 7 days. The JOABPEQ is scored with a range of 0-100 points; higher points indicate less physical disability [49]. The JOABPEQ has been found to be reliable and valid for assessing patients with LBP [50,51].

A research assistant then measured the distance between the floor and the middle fingertip during maximum lumbar forward bending, and the sEMG of the lower back was recorded. To obtain the sEMG, surface electrodes were attached to the bilateral lumbar erector spinae muscles 20 mm lateral to the L4 and L5 spinous processes [11,13,46,52] and on the hamstrings (midpoint on the line between the ischial tuberosity and the lateral epicondyle of the tibia) [53]. The sEMG was recorded using a Neuropack X1 (MEB-2306; Nihon Kohden Corporation) standing for 9 seconds, then maximum flexion for 3 seconds, and then maintaining the maximum flexion for 3 seconds, and finally a motion returning to the standing position for 3 seconds [11,13,46]. Also, the sEMG was recorded for 3 seconds in each of the following positions: back extension, right and left lateral bending, and right and left rotation of the waist.

### Intervention

#### Acupuncture Needles

Three types of double-blind needles (Confidence Co, Ltd; Figure 2) were used in this study: (1) genuine penetrating needles that pierced the skin and underlying tissue (Figure 2A; 5‐ to 20-mm depth depending on location and penetrating group), (2) skin-touch needles with a blunt tip that contacted the skin without penetration (Figure 2B; approximately 2 mm compression; skin-touch group), and (3) no-touch inert placebo needles that were designed so the tip did not contact the skin, providing a physiologically inert control condition (Figure 2C; no-touch group). From external appearance, all 3 needle types are indistinguishable. Therefore, it is not possible for participants and acupuncturists to make a judgment regarding the type of needle being used by how it looks. Also, there is silicone inside the inner guide tube that wraps around the needle and offsets the resistance to the needle insertion force [54]. This enables blinding of the participant and acupuncturist, as they cannot feel the needle type. The structure of the double-blind needles has been described in detail elsewhere [38-45,54-57]. The diameter of all 3 types of double-blind needles in this study was 0.20 mm. The penetrating needles were inserted to a depth of 5-20 mm (Table 1), depending on the anatomical location of where each needle was placed. The needles were sterilized using ethylene oxide gas prior to packaging.

**Figure 2. F2:**
[figure not shown]
Double-blind needles before (on the left) and after insertion (on the right). (**A**) Penetrating needles inserted up to a depth of 20 mm, (**B**) skin-touch needles press on the skin to a depth of 2 mm, and (**C**) no-touch inert placebo needles. The penetrating needle in the photograph shows a depth of 10 mm.

**Table 1. T1:** The acupoints’ location and insertion depth.

Acupoints	Location	Insertion depth
BL23 (Shenshu)	In the lumbar region, at the same level as the inferior border of the spinous process of the second lumbar vertebra, 1.5 cun lateral to the posterior median line.	20 mm
BL25 (Dachangshu)	In the lumbar region, at the same level as the inferior border of the spinous process of the fourth lumbar vertebra, 1.5 cun lateral to the posterior median line.	20 mm
BL26 (Guanyuanshu)	In the lumbar region, at the same level as the inferior border of the spinous process of the fifth lumbar vertebra, 1.5 cun lateral to the posterior median line.	20 mm
BL28 (Pangguanshu)	In the sacral region, at the same level as the second posterior sacral foramen, and 1.5 cun lateral to the median sacral crest.	20 mm
BL36 (Chengfu)	In the buttock region, at the midpoint of the gluteal fold.	20 mm
BL37 (Yinmen)	On the posterior aspect of the thigh, between the biceps femoris and the semitendinosus muscles, 6 cun inferior to the gluteal fold.	20 mm
BL40 (Weizhong)	On the posterior aspect of the knee, at the midpoint of the popliteal crease.	5 mm
BL52 (Zhishi)	In the lumbar region, at the same level as the inferior border of the spinous process of the second lumbar vertebra, 3 cun lateral to the posterior median line.	20 mm
BL54 (Zhibion)	In the buttock region, at the same level as the fourth posterior sacral foramen, 3 cun lateral to the median sacral crest.	10 mm
BL56 (Chengjin)	On the posterior aspect of the leg, between the 2 muscle bellies of the gastrocnemius muscle, 5 cun distal to the popliteal crease.	10 mm
BL57 (Chengshan)	On the posterior aspect of the leg, at the connecting point of the calcaneal tendon with the 2 muscle bellies of the gastrocnemius muscle.	10 mm
BL58 (Feiyang)	On the posterolateral aspect of the leg, between the inferior border of the lateral head of the gastrocnemius muscle and the calcaneal tendon, at the same level as 7 cun proximal to BL60.	5 mm
BL59 (Fuyang)	On the posterolateral aspect of the leg, between the fibula and the calcaneal tendon, at the same level as 3 cun proximal to BL60.	5 mm
BL60 (Kunlun)	On the posterolateral aspect of the ankle, in the depression between the prominence of the lateral malleolus and the calcaneal tendon.	5 mm
GB30 (Huantiao)	In the buttock region, at the junction of the lateral one-third and medial two-thirds of the line connecting the prominence of the greater trochanter with the sacral hiatus.	20 mm
GB31 (Fengshi)	On the lateral aspect of the thigh, in the depression posterior to the iliotibial band where the tip of the middle finger rests, when standing up with the arms hanging alongside the thigh.	10 mm
GB34 (Yanglingquan)	In the depression anterior and distal to the head of the fibula.	5 mm
Ex-B7 (Yaoyan)	In the lumbar region, at the same level as the inferior border of the spinous process of the fourth lumbar vertebra, 3.5 cun lateral to the posterior median line.	20 mm

#### Acupoints

BL23, BL25, BL26, BL28, BL36, BL37, BL40, BL52, BL54, BL56, BL57, BL58, BL59, BL60, GB30, GB31, GB34, and Ex-B7 (Table 1) were selected for use based on prior LBP studies [34,58-60].

#### Definition of De-Qi

Patient-perceived de-qi is suggested to be a sensation originating from deep tissues, rather than sharp pain from the lower border of the dermis as suggested by prior research [61,62]. Therefore, we defined it here as a painful sensation arising from deep tissues and asked patients whether they perceived it or not.

In addition, the de-qi perceived by the practitioner is termed “needle grasp,” suggested to be the “needle grasp sensation” felt by acupuncturists during insertion as they encounter various subcutaneous tissues [63]. However, practitioner-rated needle grasp sensation was not used as a procedural target to maintain blinding of the acupuncturists.

To standardize assessment and minimize interpretative variability, participants were asked whether they perceived a deep needling-related sensation. Additionally, the Massachusetts General Hospital Acupuncture Sensation Scale (MASS) was administered to quantitatively characterize sensory components of acupuncture needle insertion [64,65].

### Outcomes

All observed data are presented as means (SDs) and medians.

#### Primary Outcomes

The study includes 2 co-primary outcomes:

The immediate posttreatment change in the FRP measured using sEMG.The immediate posttreatment change in pain intensity measured using a 100-mm VAS.

#### Secondary Outcomes

Secondary outcomes include:

Pain intensity was measured by VAS at baseline, 24 hours, 72 hours, and one week after treatment.Physical disability assessed using the RMDQ at baseline and one week after treatment.Back pain–related quality of life assessed using the JOABPEQ at baseline and one week after treatment.Acupuncture sensation was assessed with the MASS immediately after treatment.Practitioner and participant guesses regarding needle authenticity immediately after treatment.

### Primary Objective Measurement

The sEMG was recorded from the bilateral lumbar erector spinae at L4 and L5 and on the hamstrings before and after acupuncture.

### Primary Self-Report Measurement

The intensity of LBP was evaluated on a 100 mm VAS ranging from 0 (no LBP) to 100 (the most severe LBP imaginable) at baseline, immediately posttreatment, 24 hours, 72 hours, and one week after treatment.

### Secondary Self-Report Measurement

The following validated questionnaires were used to assess physical disability and acupuncture-related sensations at the specified time points.

RMDQ: the RMDQ assesses physical disability and was completed at baseline and one week after.JOABPEQ: the JOABPEQ assesses physical disability with social life and their psychological effects, and it was completed at baseline and one week after.MASS: the MASS consists of 12 descriptors of sensations to qualify and quantify acupuncture sensations. Participants select up to 12 descriptors that describe the sensations they had during their acupuncture treatment and then rate the intensity of these sensations on a numeric rating scale (NRS) from 0 (none) to 10 (strongest imaginable). If participants felt other sensations in addition to the 12 descriptors, they wrote a description of the additional sensation and rated it on the NRS [64,65]. The MASS was completed right after the acupuncture treatment was complete.Blinding assessment: the practitioner and patient guess at the needle’s authenticity. The participants guessed whether the needle type was “penetrating,” “skin-touch,” “no-touch,” or “cannot identify the needle type” right after the acupuncture treatment was complete. The acupuncturists were also asked to guess the needle type and rated their confidence in their guess.

### Adverse Events

Even though they are rare, the research assistant and the acupuncturists monitor the participants for the presence of adverse events, such as pneumothorax, external or internal bleeding, and hematomas. Serious adverse events occurring during the study will be treated at the TAU Medical Clinic and reported to the Ethics Committee of the TAU.

The skin-touch needle features a blunt tip, a structural insertion stop, and a mechanism to physically prevent penetration and further pressure [38-45,54-57]. Previous validation studies and microscopic evaluation confirm its inability to pierce the skin under standard use [44]. Any unintended penetration would be recorded as a protocol violation and analyzed transparently.

### Treatment Procedure

Before treatment, the acupuncturist read the following script to each participant, “You are going to be randomly assigned to one of three groups: the penetrating needle group, the skin-touch needle group, or the no-touch needle group. The penetrating needle group is the treatment using real acupuncture needles that penetrate the skin, the skin-touch needle group is the treatment using skin-touch acupuncture needles that touch the skin but do not penetrate, and the no-touch needle group is the treatment with no-touch acupuncture needles with tips that do not touch the skin.” All participants were given one free real acupuncture treatment upon the return of their surveys one week later. Individuals not meeting study inclusion criteria were also offered free acupuncture.

Next, the acupuncturist asked the participant to point out the most severe stiffness or pain in the lumbar, gluteal, and posterior thigh regions. Participants then lay supine on a treatment table.

Before each needle application, the acupuncturist massaged each acupoint with the fingertip of the index finger of the nondominant hand in a circular motion for 2 seconds. This insertion technique is a commonly practiced method in Japanese-style acupuncture. The assistant peeled off the adhesive paper covering the bottom of the pedestal of each needle device, covered the needle with an outer guide tube, and handed it to the acupuncturist. Then, the acupuncturist placed the needle device on the acupoint, which was held in place by the adhesive. The acupuncturist stabilized the needle device with the nondominant hand and tapped the top of the needle handle, which protruded from the outer guide tube, 5-7 times using the index finger of the dominant hand [66].

After needle tapping-in, the acupuncturist removed the outer guide tube and inserted the needle further to its targeted depth by rotating it clockwise and counterclockwise using an alternating twirling technique [38-45,54,66]. This process was repeated until all needles were inserted. The needles were retained for 15 minutes.

After 15 minutes, the acupuncturist withdrew each needle to its initial position using an alternating twirling technique to remove them [38-45,54,66]. The needle was then stored in an opaque envelope to prevent the group allocation from being revealed. After all needles were removed, the research assistant checked for bleeding from each needled insertion site and wiped the blood away with a cotton ball and/or applied pressure if needed. The acupuncturist again massaged the area where the needle was inserted.

Then, the acupuncturist assessed the participant for back pain. If the participant had no pain, the treatment was complete. If the participant still had pain, the hardest indurations and the most tender areas in the lumbar erector spinae, quadratus lumborum, gluteus medius, and biceps femoris were treated using a Sparrow Pecking technique (rapidly inserting and withdrawing the needle tip within a 2 mm amplitude) using another needle from the same set of needles randomly assigned to the participant [13].

After the acupuncture treatment was complete, participants rated the intensity of their LBP on a 100 mm VAS. Participants then completed the MASS. The participants then guessed whether the treatment was “penetrating,” “skin-touch,” “no-touch,” or “cannot identify the needle type.” They reported their confidence level in their guesses on a 100 mm VAS ranging from 0 (no confidence) to 100 (full confidence) [37-43,52,63]. The acupuncturists were also asked to guess the needle type and rated their confidence in their guess. The sEMG of the lower back was recorded using the same procedure as before the intervention. One week after treatment, participants brought the completed questionnaires (intensity of LBP on VAS, RMDQ, and JOABPEQ) back to the Acupuncture Clinic. At that time, a research assistant offered them a free acupuncture treatment with regular acupuncture needles.

### Recruitment

Seven licensed, experienced acupuncturists (4 are listed as authors: [name]) with more than 5 years of experience each, at TAU Acupuncture Clinic, administered the acupuncture treatments. We enrolled 75 participants with CNSLBP. Participants were recruited by advertisements listed on TAU websites, flyers placed on TAU campus notice boards, and at public facilities (city offices, gymnasiums, and surrounding high-rise apartment buildings). The advertisements provided a brief introduction to the study, a description of the target population with eligibility criteria, and study contact information. Participant recruitment began in October 2018.

### Statistical Analysis

Baseline characteristics will be assessed using Fisher exact test, ANOVA, and the Levene test. To evaluate the primary and secondary outcomes, we will use a linear mixed-effects model to account for the variability between groups and over time. This model will include “treatment group,” “time,” and their interaction as fixed effects. To address the potential influence of practitioner-related differences, “practitioner ID” will be included as a random effect. For post-hoc analyses, the Bonferroni correction will be applied to adjust for multiple comparisons. For nonnormally distributed data, the Mann-Whitney *U* test, Friedman test, or Kruskal-Wallis test will be used as appropriate. Blinding success will be evaluated by comparing the proportion of correct guesses in each group against chance level (33.3%) using a chi-square goodness-of-fit test. In addition, Bang Blinding Index will be calculated for both participants and acupuncturists to quantify the degree of blinding [55,57]. A Blinding Index close to 0 indicates successful blinding, whereas values approaching ±1 indicate unblinding. To account for variability among acupuncturists, analyses will be conducted under an intention-to-treat framework. Missing outcome data will be handled using multiple imputation under the assumption of missing at random. All statistical analyses will be conducted using SPSS Statistics version 31 (IBM SPSS Statistics) and R (R Foundation for Statistical Computing). Statistical significance will be set at a 2-sided *P* value of <.05.

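### For the two co-primary immediate changes, the stated group-by-time model gives an unbiased but less precise raw-change contrast; adjusting for baseline and naming the immediate-time VAS contrast would be a free improvement

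*Protocol article*

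**What the plan says.** The Primary Outcomes section of the protocol article defines two co-primary outcomes, "The immediate posttreatment change in the FRP measured using sEMG" and "The immediate posttreatment change in pain intensity measured using a 100-mm VAS".

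They differ in their measurement times. Under Primary Objective Measurement, surface EMG is recorded from the erector spinae and "on the hamstrings before and after acupuncture", so FRP has two times. Under Primary Self-Report Measurement, VAS is taken "at baseline, immediately posttreatment, 24 hours, 72 hours, and one week after treatment", so it has five. The three later VAS times are secondary: "Pain intensity was measured by VAS at baseline, 24 hours, 72 hours, and one week after treatment".

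The Statistical Analysis section uses one approach throughout: "To evaluate the primary and secondary outcomes, we will use a linear mixed-effects model". On its content: "This model will include “treatment group,” “time,” and their interaction as fixed effects". The only random effect named is for the practitioner. No baseline covariate is listed, and the section does not say which contrast tests a co-primary outcome. Pairwise comparisons appear only as post-hoc analyses with Bonferroni correction.

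**The concern.** Baseline is a measured occasion for both outcomes, so on the natural reading it is a level of time with its own free mean in each arm. The treatment effect at the immediate time is then the difference between arms in mean change. That subtracts baseline with a coefficient of exactly 1. The regression of post on baseline usually has a smaller slope, so part of the baseline noise is carried into the estimate. With 25 participants per arm, the baseline already collected could be used better.

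A second matter concerns VAS alone. An interaction test over five times pools the immediate change with changes at 24 hours, 72 hours and one week. If that test were read as the primary result, a difference arising only at secondary times could be reported as success on a co-primary outcome that shows none.

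**Working it through.** **Inputs from the protocol article.** Sample Size: effect size 0.51 (metric not named), power 95%, alpha 5%, 63 participants (21 per group), 75 recruited. Randomization: 1:1:1. Measurement times as described above. The baseline-to-post correlation rho is not given; I assume 0.3 to 0.8.

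**Step 1: the plan's own figure.** One-way ANOVA, three groups, 0.51 read as Cohen's f, noncentrality f² × N = 0.2601 × 63 = 16.39 on 2 and 60 degrees of freedom. Power is 0.952, and 63 is the smallest N reaching 95%. The stated figure reproduces. At N = 75 power is 0.979.

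**Step 2: precision.** With SD σ at both times:
- variance of change: 2σ²(1 − rho)
- residual variance after baseline adjustment: σ²(1 − rho²)
- ratio: (1 − rho²) / (2(1 − rho)) = (1 + rho)/2

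The direction does not need equal SDs. With σ0 at baseline and σ1 after treatment, the change variance minus the adjusted variance is (σ0 − rho·σ1)², which is never negative.

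**Step 3: effect on power**, with f = 0.51 on the change scale, f divided by √((1 + rho)/2) for the adjusted analysis, and one degree of freedom lost:

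| rho (assumed) | Variance ratio | N for equal precision, instead of 63 | Power at 63: change → adjusted | Power at 75: change → adjusted |
|---|---|---|---|---|
| 0.3 | 0.65 | 41 | 0.952 → 0.995 | 0.979 → 0.999 |
| 0.5 | 0.75 | 47 | 0.952 → 0.988 | 0.979 → 0.996 |
| 0.7 | 0.85 | 54 | 0.952 → 0.976 | 0.979 → 0.992 |
| 0.8 | 0.90 | 57 | 0.952 → 0.969 | 0.979 → 0.988 |

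A simulation at N = 63 (3,000 runs per setting) agrees: adjusted power 0.995, 0.985, 0.973 and 0.964; both methods hold size near 5%.

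**Step 4: FRP.** With two times and participants as blocks, the interaction has 2 × 1 = 2 degrees of freedom and is the one-way comparison of changes. In a simulated data set both F statistics were 6.7102. For FRP the interaction tests the co-primary outcome itself.

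**Step 5: VAS.** The all-times interaction has 2 × 4 = 8 degrees of freedom; the immediate contrast has 2. I used noncentral chi-square with known covariance, N = 63, one arm differing from the other two by 0.51 × 3/√2 = 1.08 SDs of the immediate change, rho 0.5 or 0.7, and compound symmetry or AR(1). Profiles are multiples of that effect at the four post-treatment times and are assumptions:

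| Profile | Immediate contrast (2 df) | All-times interaction (8 df) |
|---|---|---|
| Later only (0, 0, 0.5, 1) | 0.05 | 0.61 to 0.98 |
| Immediate only (1, 0, 0, 0) | 0.961 | 0.975 to 0.985 |
| Decaying (1, 0.5, 0.25, 0) | 0.961 | 0.91 to 0.95 |
| Constant (1, 1, 1, 1) | 0.961 | 0.86 to 0.975 |

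(The value 0.961 exceeds 0.952 because the covariance is taken as known.) The 8-df test answers a different question; it is not uniformly weaker.

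**The case against.** The strongest reply is that nothing stated is invalid. The outcome is defined as a change, so analysing change matches it, and under randomisation the contrast is unbiased. At the plan's own effect size the power target is met without adjustment. All of that stands. The choice is between two valid estimators, and the gain at 75 participants is 1 to 2 percentage points of power at f = 0.51 and 0.979 as the starting point. A larger gain needs a smaller true effect. For example, a shift of 0.8 SD in one arm at rho 0.5 is f = 0.8 × (√2/3)/√(2 × 0.5) = 0.38, and power at 75 then goes from 0.825 to 0.921; that effect lies well below the design value.

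The second reply is that the article lists the interaction as a model term and never makes its omnibus test the primary one. The immediate contrast can be taken from the same model, and a statistical analysis plan that is not shown may name it. This also stands, and it makes the VAS point conditional. It does not remove the precision point, because a contrast drawn from the unconstrained model is still a raw-change comparison.

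Third, data collection ended in March 2025, so a change is harmless only if made before results by arm are seen. That belongs in the fix.

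**Conclusion.** The point holds as an efficiency improvement. If baseline is a level of time and within-participant correlation is modelled, the stated model gives an unbiased immediate contrast whose variance is 1.11 to 1.54 times that of the baseline-adjusted one (rho 0.8 to 0.3, assumed; equal variances). This applies to FRP and VAS alike. The need to name the immediate contrast applies to VAS only, and matters only if the all-times interaction would otherwise serve as the primary test.

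Four stronger readings are tempting, and the documents do not support them:
- **That the plan tests an all-times interaction for both endpoints.** The Statistical Analysis section does not say so, and FRP has only two times.
- **That an immediate-only effect would be diluted.** In that case the 8-df test has slightly more power (0.975 to 0.985 against 0.961).
- **That the estimate is biased by leaving out baseline.** The contrast subtracts baseline; the cost is precision.
- **That the trial falls short of its planned power for this reason.** With 0.51 read as Cohen's f on the change scale, the target is met at 63.

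**What to change.** Before outcomes by arm are examined, add a dated clarification to the Statistical Analysis section with three elements:

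1. For each co-primary outcome, the primary estimate is the arm contrast at the immediate post-treatment time, adjusted for that outcome's baseline value. Either enter baseline as a covariate with the immediate value as outcome, or use a mixed model whose baseline mean is constrained to be common to the arms. The practitioner random effect stays.
2. For VAS, this immediate-time contrast is the primary test; contrasts at 24 hours, 72 hours and one week are secondary and can come from the same model.
3. For FRP no change of hypothesis is needed, since the two-time interaction already tests the co-primary outcome; only the baseline adjustment is added.

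The cost is a few sentences and re-coding of the model. Every value required is already collected. If results by arm have already been seen, report the planned analysis as primary and the adjusted one as a labelled sensitivity analysis.

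### The mixed model names practitioner as its one random effect and gives no participant term, so the test of the co-primary change has too large a standard error and loses power

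*Protocol article*

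**What the plan says.** The Statistical Analysis section covers all outcomes with one model: "To evaluate the primary and secondary outcomes, we will use a linear mixed-effects model to account for the variability between groups and over time". It lists the fixed part: "This model will include “treatment group,” “time,” and their interaction as fixed effects". It then gives the random part and its purpose: "To address the potential influence of practitioner-related differences, “practitioner ID” will be included as a random effect". No other random effect, subject identifier or residual covariance appears anywhere in the article.

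The outcomes are repeated on the same people:

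- sEMG (Primary Objective Measurement): recorded from the erector spinae and "on the hamstrings before and after acupuncture", so twice.
- VAS (Primary Self-Report Measurement): "at baseline, immediately posttreatment, 24 hours, 72 hours, and one week after treatment", so five times.
- RMDQ (Secondary Outcomes): "Physical disability assessed using the RMDQ at baseline and one week after treatment", so twice. JOABPEQ has the same schedule.

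Under Primary Outcomes, both co-primaries are defined as the change immediately after treatment. Under Recruitment, treatment was given by "Seven licensed, experienced acupuncturists".

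**The concern.** With group, time and their interaction in the model, a between-arm difference in change is the group-by-time contrast. Its precision depends on how strongly the two values from one person are correlated, because that correlation cancels stable differences between people. A practitioner intercept does not do this. It links all patients of one acupuncturist equally and links a person's own two values no more closely than that. With seven practitioners and 75 participants it cannot stand in for the participant level.

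The model as stated therefore tests change against the variance between people within a practitioner, not against the smaller variance of change within a person. What is at stake is a missed effect on either co-primary. The Sample Size section chose 95% power expressly to limit type II error, and this error term works against that choice.

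**Working it through.** **The plan's own figure.** The stated sample size is 63 (21 per group), from an effect size of 0.51, 95% power and 5% alpha. It reproduces as a one-way ANOVA on three groups with 0.51 read as Cohen's f: noncentral F with lambda = f² × N = 0.51² × 63, on 2 and 60 degrees of freedom, gives power 95.2%, and 60 participants give 94.1%. The figure of 63 does not depend on the point raised here.

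**Inputs.** n = 25 per arm, 7 practitioners and two-sided alpha 0.05 are from the article. The within-person correlation rho is not given; a range of 0.3 to 0.9 is assumed, with equal variance s² at each time after practitioner differences are removed.

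**Standard error of the between-arm difference in change.**

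- True variance: 4s²(1-rho)/n.
- Variance used by the model as written: 4s²/n.
- Ratio of model SE to true SE: 1/sqrt(1-rho).

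| rho (assumed) | SE ratio | actual level of a nominal 5% contrast |
|---|---|---|
| 0.3 | 1.20 | 1.9% |
| 0.5 | 1.41 | 0.56% |
| 0.7 | 1.83 | 0.035% |
| 0.9 | 3.16 | about 0% |

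**One worked case: rho = 0.6, effect 0.7 SD, 25 per arm (normal approximation, s = 1).**

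- True SE = sqrt(4 × 0.4/25) = 0.253. Model SE = sqrt(4/25) = 0.400. Ratio 1.58.
- The model rejects when the estimate exceeds 1.96 × 0.400 = 0.784, which is 0.784/0.253 = 3.10 true SEs. Type I error is about 0.19%.
- The effect is 0.7/0.253 = 2.77 true SEs. Power as written: Phi(2.77 - 3.10) = about 37%. Power with pairing respected: Phi(2.77 - 1.96) = about 79%.

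**Simulation.** 75 participants, 7 practitioners, one pre and one post value, 4000 runs, rho = 0.5. Practitioner was fitted as a fixed effect, as an approximation to the random intercept.

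| | Practitioner term only | Participant pairing respected |
|---|---|---|
| Mean model SE (true SD of the estimate 0.281) | 0.395 | 0.282 |
| Type I error | 0.7% | 5.1% |
| Power, 0.6 SD effect | 25% | 55% |

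**Against the planned power.** If f = 0.51 is taken to apply to the change score, the omnibus interaction test at N = 63 has about 95% power with a participant term. Without it, power is about 88%, 74% and 38% at rho = 0.3, 0.5 and 0.7.

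**Other contrasts under the same model.**

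- Group effect averaged over m times: ratio of model SE to true SE is 1/sqrt(1+(m-1)rho), so the SE is too small. Over rho 0.3 to 0.9 the ratio is 0.88 to 0.73 for two times (pairwise type I error 8.6% to 15.5%) and 0.67 to 0.47 for five times (18.6% to 36.1%).
- Between-arm contrast at a single time: the true and the model variance are both 2s²/n. Simulated pairwise type I error, with no practitioner effect and rho 0.5 and 0.7, was 4.9% to 5.5%.
- MASS and the needle guesses are measured once and are not affected.

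**The case against.** The best defence is that the text never says practitioner is the only random effect. The sentence explains why one term is included, and a condensed article may leave the within-participant covariance to an analysis plan that is not shown. A residual covariance by participant is not a random effect, so a sentence about random effects does not rule it out. The section also says that the model is meant to handle variability over time, and its nonparametric list includes the Friedman test, which blocks on the participant. The authors may have taken the participant level for granted.

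This stands in part. An unshown plan could contain the missing term, and the text must not be read as excluding it. But the article does not leave the random structure for later: it states it, gives a reason and names one level, which is not the level at which the data repeat. Variability between groups and over time is what the fixed effects describe. The Friedman test belongs to a separate fallback and puts no participant term into the model.

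Two stronger readings should be resisted. A reader might infer that the trial risks false-positive efficacy claims. The inflated error belongs to a group main effect averaged over times, including the pre-treatment baseline; the Primary Outcomes section defines both co-primaries as change, where the error runs the other way. A reader might also infer that every standard error in the trial is wrong and that all values are treated as fully independent. They are independent given practitioner, and single-time contrasts between arms are essentially right.

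**Conclusion.** The point holds for the model as written. The participant level is missing from the stated model for every repeated outcome, and for both co-primaries this makes the test of change conservative. The loss is substantial at plausible correlations: an SE inflated by 1.20 to 3.16 for rho from 0.3 to 0.9, and in the worked case power of about 37% against about 79%.

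These sizes rest on an assumed rho, equal variances over time and an assumed effect; with rho near zero the loss would vanish. The direction for the change contrast does not depend on the exact value as long as rho is positive. The harm to the primary question is a possible missed effect, not a spurious one. The conclusion falls away if an analysis plan that is not shown already specifies a participant term.

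**What to change.** State the participant level in the model: either a participant random intercept or an unstructured within-participant residual covariance, in addition to the practitioner random effect. With only two measurement times, either choice brings the test of change back to within-person variance. For the five VAS times the unstructured form also avoids assuming equal correlation between all pairs of times.

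The cost is one sentence. Data collection is complete, but the Statistical Analysis section describes the analysis in the future tense, so the model can be corrected before it is run. No new data, participants or measurements are needed, and the sample size of 63 is unchanged. If the full analysis plan already contains the term, the article's sentence should be brought into line with it.
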